**<Proper facedown positioning>**

- Lying on the bed, prone relaxed position
- Modified prone relaxation posture (head bowed position on the table, head bowed position on the bed)
- Standing and prone relaxed using a walker

**<Facedown Exercise>**

- Arms and Legs Exercises in a Bed Position
- Exercising in a four-legged position lying on the bed (back stretch)
- Walking in place from a prone position using a walker

After surgery, the pain score in numeric rating scale will be evaluated immediately after the surgery. The patients will perform the trained posture and exercise three times daily, and the exercise therapist will revisit on the postoperative day 1 to give feedback on posture and exercise. The pain score at the back neck, shoulder and lower back will be evaluated on the postoperative day 1, 2, and 3. There will be no difference in the treatment process other than using rehabilitation exercise therapy during the prone period. Patients will stay in the hospital until the postoperative day 3 and then be discharged. The trial will end on the day 5 (postoperative day 3) as the patients discharged from the hospital.

**Overview of the schedule of the clinical trial.**

|                           | Day 1
(Admission) | Day 2
(Surgery) | Day 3
(POD 1) | Day 4
(POD 2) | Day 5
(POD 3) |
|---------------------------|------------------------------|----------------------------|--------------------------|--------------------------|--------------------------|
| Eligibility determination | X                            |                            |                          |                          |                          |
| Informed consent          | X                            |                            |                          |                          |                          |

|                                                                                           |   |                         |   |   |   |
|-------------------------------------------------------------------------------------------|---|-------------------------|---|---|---|
| Randomization                                                                             | X |                         |   |   |   |
| Medical & Ophthalmic History                                                              | X |                         |   |   |   |
| Maintain facedown posture                                                                 |   | X
(after
surgery) | X | X | X |
| Pain assessment                                                                           |   | X
(after
surgery) | X | X | X |
| Exercise training by exercise therapist (with brochure and movie clip) for exercise group |   | X                       | X |   |   |
| Three times of daily exercise for exercise group                                          |   | X
(after
surgery) | X | X | X |
| Patient satisfaction questionnaire for exercise group                                     |   |                         |   |   | X |

## 12. Clinical evaluation items and observation test method

Pre-operative data collection:

- Demographic data
- Laterality
- Comorbid systemic diseases (diabetes mellitus, arterial hypertension, etc.)
- Indication for vitrectomy
- previous history of ocular surgery
- combined cataract surgery
- methods of anesthesia

Post-operative data collection:

- Intraocular fillings (SF6, C3F8, Silicon oil)

- Operative time
- Pain scores measured by numeric rating scale at back neck, shoulder, and lower back
  - Pain scores will be measured on the surgery day and the postoperative day 1, 2, and 3.
- Patient satisfaction questionnaire for exercise group on the postoperative day 3.

### 13. Predicted side effects

In this study, there is no additional side effect to be predicted because the existing retinal surgery and prone position prescription proceed in the same manner except for the education and implementation of exercise therapy that can be combined with the prone position during hospitalization.

### 14. Outcome measures and statistical analysis

#### 14.1. Primary outcome

Pain score measured by numeric rating scale at back neck, shoulder, and lower back on the postoperative day 3. Numeric rating scale is a score that measures pain. If there is no pain, it is marked as 0, and if the pain is the worst possible pain, it is measured as 10.

[figure not shown]

#### 14.2. Secondary outcome measures

- 1) Pain score measured by numeric rating scale at back neck, shoulder, and lower back immediate after the surgery.
- 2) Pain score measured by numeric rating scale at back neck, shoulder, and lower back on the postoperative day 1.
- 3) Pain score measured by numeric rating scale at back neck, shoulder, and lower back on the postoperative day 2.
- 4) Difference between the study groups in pain score change over time at back neck, shoulder, and lower back

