#### **9.4 Sample size calculation**

No relevant studies have previously described the effect of structured exercise on FDP related pain. There has been only one study that evaluated FDP related pain quantitatively. A randomized controlled study performed by Adachi et al. reported the effects of aromatherapy massage on FDP related pain after vitrectomy. Based on the clinical assumption that structured exercise program would have comparable or greater effect on FDP related pain, we conducted a sample size calculation using data from the previous report. We conducted a sample size calculation expecting an effect size of 0.9 based on post-treatment back pain score in aromatherapy group and control group of the previous study. The estimated sample size was 32 patients per group to detect differences between two groups at 90% power and a significance level of 0.05. Considering a 10 % loss to follow-up, we are aiming to recruit 35 patients in each arm.

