## 11. Research method

This study is for patients who are going to be prescribed facedown posture after retinal surgery.

Participating the study or not will not influence the clinical decision and surgical procedure, but only a pain assessment in the back neck, shoulder, and lower back will be additionally performed every day after the surgery for the study participants. Those who are assigned to the exercise group will additionally be instructed for a structured exercise program designed to keep the prone posture easily and to relieve musculoskeletal pain. The exercise group will be trained by an exercise therapist. All inpatient care and surgical procedures other than learning and performing rehabilitation exercise will be the same in both study groups.

| Control group                                                                                      | Exercise group                                                                                                                                                              |
|----------------------------------------------------------------------------------------------------|-----------------------------------------------------------------------------------------------------------------------------------------------------------------------------|
| After surgery, take and maintain facedown posture without getting additional training or exercise. | After surgery, subjects will be trained for a structured exercise routine by an exercise therapist and perform the exercise according to the instruction three times a day. |
| Pain assessment will be performed every day after surgery.                                         |                                                                                                                                                                             |

All patients scheduled for vitreoretinal surgery for macular hole or retinal detachment is going to be admitted to the hospital the day before surgery (day 1). On the day 1, every patients will be evaluated for their eligibility, and those who are eligible candidates will be provided with information about the trial and invited to participate. They will be given enough time to consider their decision and the opportunity to ask questions. After informed consent is obtained, subjects will be randomized.

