On the day of the retinal surgery, an exercise therapist who is affiliated to the Department of physical and rehabilitation medicine, Samsung Medical Center, will visits before surgery to educate the structured

rehabilitation exercise program. Details of a structured exercise program for the exercise group is as follow.

Rehabilitation exercise education consists of **(1) proper facedown positioning**, which would assist patients to maintain the prone position more easily and stably without giving too much stress to the body, and **(2) facedown exercise**, which would reduce the burden on muscle and joints induced by the facedown posture and enhance muscle strength to withstand the stress applied by the facedown posture.

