**14.3. Statistical analysis**

Descriptive statistics for continuous variables will be presented in terms of mean, median, standard deviation, interquartile range, minimum and maximum values, and descriptive statistics for categorical variables are presented in terms of frequencies and ratios belonging to each category.

The comparison of continuous variables between the two groups will be tested with the two-sample t-test or Wilcoxon's rank sum test depending on whether the data are normal, and the comparison of categorical variables will be tested with the Chi-square test or Fisher's exact test. Since there will be three site for pain scoring, the statistical significance will be set at  $p < 0.017$  (0.05 divided by 3, Bonferroni's method) to control the inflation in the size of the type 1 error.

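### No pain score precedes randomisation or training: the unadjusted POD 3 comparison gives up precision, outcome 4 has no clear origin, and outcome 1 can hardly show an exercise effect

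*Protocol*

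**What the plan says.** Section 12 lists no pain score among the pre-operative data. Under post-operative data it states: "Pain scores will be measured on the surgery day and the postoperative day 1, 2, and 3". The schedule in Section 11 agrees: randomisation falls on Day 1, and the first pain assessment is on Day 2, marked as after surgery.

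Section 14.1 makes the POD 3 score at three sites the primary outcome. Section 14.2 lists as outcome 1 "Pain score measured by numeric rating scale at back neck, shoulder, and lower back immediate after the surgery" and as outcome 4 "Difference between the study groups in pain score change over time at back neck, shoulder, and lower back". It gives no reference time for the change.

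For continuous variables, Section 14.3 names the "two-sample t-test or Wilcoxon's rank sum test depending on whether the data are normal", at p < 0.017 per site. It names no covariate.

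Section 11 times the training in two ways. The text says the therapist "will visits before surgery to educate the structured" programme on the day of surgery. The group table says "After surgery, subjects will be trained for a structured exercise routine by an exercise therapist".

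**The concern.** A score taken before randomisation cannot have been influenced by allocation. It explains part of the spread in later pain, and it gives change over time a fixed origin. This trial has no such score. An analysis plan cannot repair that, because it cannot adjust for a measurement that was never made.

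Three things follow.

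- The POD 3 comparison carries all the between-patient variation in pain, with nothing to remove any of it.
- The only available origin for outcome 4 is the immediate post-operative score, which is itself outcome 1.
- Outcome 1 is compared between arms before the scheduled exercise has had a chance to act. A difference there could reflect chance, knowledge of allocation (Section 9.6 says participants are not masked) or teaching before surgery, but hardly exercise.

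**Working it through.** **Inputs.** From Section 9.4: "expecting an effect size of 0.9 based on post-treatment back pain score in aromatherapy group and control group", and "The estimated sample size was 32 patients per group to detect differences between two groups at 90% power and a significance level of 0.05". From Section 14.3: 0.017 per site. The correlation ρ between Day 1 and POD 3 pain is not in the Protocol; 0.2 to 0.5 is assumed. Two-sided tests are also assumed, because the sample size section does not state sidedness.

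**Reproducing the plan's 32.** For d = 0.9, 90% power and two-sided 0.05, the normal approximation is n = 2(1.960 + 1.282)²/0.9² = 25.9, so 26 per group. The noncentral t calculation gives 27. A Wilcoxon calculation with the minimum asymptotic relative efficiency of 0.864 gives exactly 32. The stated figure is therefore reproducible as a rank-sum calculation at 0.05. That the analysis uses 0.017 instead is a separate matter; here it only sets the threshold for power.

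**Effect of adjustment.** Analysis of covariance on a baseline score multiplies the residual SD by √(1 − ρ²), so the standardised effect becomes d/√(1 − ρ²). With 32 per arm the noncentrality is [d/√(1 − ρ²)] × √(32/2) = 4d/√(1 − ρ²). Power is from the noncentral t on 62 degrees of freedom, ignoring the one lost to the covariate, at two-sided 0.017.

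| Assumed ρ | Residual variance | Noncentrality, d = 0.9 | Power, d = 0.9 | Power, d = 0.6 (assumed) |
|---|---|---|---|---|
| 0 (unadjusted) | 1.00 | 3.60 | 87.1% | 48.3% |
| 0.2 | 0.96 | 3.67 | 88.5% | 50.3% |
| 0.3 | 0.91 | 3.77 | 90.3% | 52.8% |
| 0.5 | 0.75 | 4.16 | 95.3% | 62.6% |

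At d = 0.9 the gain is about 1.5, 3.2 and 8.2 percentage points.

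**Is the unadjusted comparison biased?** The standard error of a chance baseline difference is √(2/32) = 0.25 SD, so a difference larger than that arises in about one trial in three. Only the fraction ρ carries over: at ρ = 0.3, 0.3 × 0.25 = 0.075 SD, against a planned effect of 0.9 SD. The t-test's standard error already allows for it. In 50,000 simulated null trials with 32 per arm and ρ = 0.5, the unadjusted t-test rejected in 0.0177 of trials at nominal 0.017. The simulation error is √(0.017 × 0.983/50,000) = 0.0006. The mean difference was −0.0008 SD. There is no bias.

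**Order of events on Day 2.**

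| Event | Where stated | Timing |
|---|---|---|
| Training | Section 11, text | Before surgery |
| Training | Section 11, group table | After surgery |
| Training | Section 11, schedule | Day 2, no time given; again on POD 1 |
| First pain score | Section 11, text and schedule | Immediately after surgery |
| Daily exercise | Section 11, schedule | Day 2, after surgery |

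On either account the first score follows randomisation and surgery. Whether it also follows training depends on which account is used.

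**The case against.** The strongest reply is that randomisation protects the primary comparison. It does. A reader might infer that without a baseline the POD 3 result mixes starting pain with treatment effect; the calculation above shows that it does not. The confusion is confined to outcomes 1 and 4.

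Second, the gain rests on a correlation that nobody has supplied. Section 9.2 excludes pre-existing musculoskeletal disorder, and a Day 1 score comes before any facedown posture. Scores could sit near zero with little spread, and ρ would then be low. This stands, and it is why ρ = 0.2 belongs in the table.

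Third, covariates and models are commonly left to the analysis plan, which is not at hand. This stands for the detail: the Protocol is not at fault for lacking a mixed model or a covariate list. It does not cover the assessment schedule, which the Protocol fixes, and Section 14.3 positively names the unadjusted tests.

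Fourth, if no exercise precedes the immediate score, that score might serve as the baseline. The Protocol does not support this safely. The score is post-randomisation, comes from unmasked participants and, on one of the two timings, follows training. Adjusting for it could remove part of an effect of training.

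Fifth, the group table may simply be loosely worded, since a second training session does follow on POD 1. That is plausible, but the two statements still differ on the first session. Finally, Section 14.2 lists outcome 1 without claiming that it shows an exercise effect. That is true, so the remedy is to label it descriptive.

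**Conclusion.** The point holds as a loss of precision in the primary comparison and a lack of clarity in two secondary outcomes. It is not a bias in the primary result. At the plan's own effect size and 0.017 threshold, 32 per arm give 87.1% power by t-test. A Day 1 covariate would raise this to 88.5%, 90.3% or 95.3% at assumed correlations of 0.2, 0.3 or 0.5. A correlation of 0.3 would bring power back to the planned 90% without another patient, while one of 0.2 or less would add little.

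The absence of bias assumes that everyone randomised is analysed. Sections 9.3(1) and 9.3(2) define dropout by exercise performance, which can apply only to the exercise arm. If such patients were left out, a Day 1 score would be the only pre-randomisation check on whether those remaining had comparable pain.

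Outcome 1 should not be read as evidence about exercise, and outcome 4 needs a stated origin. The Protocol does not settle whether the immediate score comes before or after training, so neither reading should be taken as established.

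**What to change.** - Add a pain score at the three sites on Day 1, before randomisation, to Section 12 and the schedule.
- In Section 14.3, make the per-site POD 3 comparison a baseline-adjusted one, for example analysis of covariance on the Day 1 score. Adjust for the score rather than subtract it: a change score has variance 2(1 − ρ) relative to the raw score, which is 1.4 at ρ = 0.3. It would need 47 per group for 90% power at 0.017, against 34 unadjusted and 31 adjusted (normal approximation).
- Name the Day 1 score as the reference for outcome 4. The model can be left to the analysis plan.
- Report the immediate post-operative score descriptively. If it is ever used as a covariate, state that it is post-randomisation, unmasked and possibly post-training.
- Reconcile the training time in the text and the group table of Section 11.

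The cost is one brief extra assessment for patients already admitted and giving their history that day, one line on the case report form, and changes of wording. The sample size need not change for this point.

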**5) Patient's satisfaction on the structured exercise program.**

The exercise group will be asked to answer the patients satisfaction questionnaire. The questionnaire items will be as follow.

(1) The rehabilitation program help patients recover health.

1: strongly disagree 2: disagree 3: neither agree nor disagree 4: agree 5: strongly agree

(2) I want this exercise program the next time I have retinal surgery

1: strongly disagree 2: disagree 3: neither agree nor disagree 4: agree 5: strongly agree

(3) I would recommend this program to other patients getting retinal surgery

1: strongly disagree 2: disagree 3: neither agree nor disagree 4: agree 5: strongly agree

(4) Overall satisfaction

1: very disappointed 2: disappointed 3: neither satisfied nor disappointed 4: satisfied 5: very satisfied

**14.3. Statistical analysis**

Descriptive statistics for continuous variables will be presented in terms of mean, median, standard deviation, interquartile range, minimum and maximum values, and descriptive statistics for categorical variables are presented in terms of frequencies and ratios belonging to each category.

The comparison of continuous variables between the two groups will be tested with the two-sample t-test or Wilcoxon's rank sum test depending on whether the data are normal, and the comparison of categorical variables will be tested with the Chi-square test or Fisher's exact test. Since there will be three site for pain scoring, the statistical significance will be set at  $p < 0.017$  (0.05 divided by 3, Bonferroni's method) to control the inflation in the size of the type 1 error.

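### Single-step Bonferroni over the three pain sites is valid, but Holm's procedure has more power for the second and third site within the same 5% family-wise limit

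*Protocol*

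**What the plan says.** Protocol section 14.1 defines the primary outcome as "Pain score measured by numeric rating scale at back neck, shoulder, and lower back on the postoperative day 3". That makes three primary comparisons. The section does not say whether success means any site or all sites.

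Section 14.3 handles the multiplicity with one threshold: "Since there will be three site for pain scoring, the statistical significance will be set at" p < 0.017. The derivation and reason follow: "0.05 divided by 3, Bonferroni's method) to control the inflation in the size of the type 1 error". No stepwise procedure is mentioned. The comparisons are two-sample t-tests or Wilcoxon rank sum tests.

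Section 14.2 lists pain at the same three sites immediately after surgery and on postoperative days 1 and 2 as secondary outcomes, together with the group difference in change over time.

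Section 9.4 sizes the trial "to detect differences between two groups at 90% power and a significance level of 0.05", "expecting an effect size of 0.9 based on post-treatment back pain score in aromatherapy group and control group". It concludes: "The estimated sample size was 32 patients per group", with 35 per arm to be recruited.

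**The concern.** Under single-step Bonferroni every site must reach 0.05/3, even after another site has already been shown to differ. Once one null hypothesis has been rejected, at most two true ones remain, so holding the rest to 0.05/3 is stricter than a 5% family-wise error requires. Holm's procedure uses that slack.

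This matters because section 14.1 names all three sites as primary, so the verdict at each site counts. The planned 90% power was calculated at 0.05, while each site is tested at about one third of that. If the programme works at all three sites, which is what section 7.1 hopes for, the fixed threshold makes it more likely that one or two real effects are reported as non-significant.

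**Working it through.** **Inputs.** From the protocol: effect size 0.9, 90% power, significance level 0.05, 32 per group and 35 recruited (section 9.4); three sites on day 3 (section 14.1); threshold 0.05/3 (section 14.3). Assumed, because the protocol gives no figure: two-sided tests, effect sizes by site, and correlation between sites (range shown).

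**The plan's own figure.** The normal approximation is n = 2(z₁₋α/₂ + z₁₋β)²/d².
- At two-sided 0.05: 2(1.960 + 1.282)²/0.81 = 25.9, so 26 per group. The exact t-test gives 27.
- At two-sided 0.05/3: 34 by the normal approximation, 35 by the t-test.
- The stated 32 matches neither. It comes out for a Wilcoxon test at its worst-case efficiency of 0.864 (26.94/0.864 = 31.2, rounded up), or for a t-test at two-sided 0.025 (31.9). Neither is stated. The point does not depend on how 32 was reached, so 32 is taken as given.

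**Power of one t-test at d = 0.9.** The noncentrality at 32 per group is 0.9 × √(32/2) = 3.6.

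| n per group | α = 0.05 | α = 0.05/3 |
|---|---|---|
| 32 | 94.3% | 86.9% |
| 35 | 96.0% | 90.2% |

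**The two procedures.** Bonferroni rejects each site with p ≤ 0.05/3. Holm compares the smallest p with 0.05/3, the next with 0.05/2 and the largest with 0.05, and stops at the first failure.
- Holm's thresholds are never lower than Bonferroni's, so it rejects at least the same sites.
- The first step is the same, so the chance of at least one rejection is the same.
- With m₀ true null hypotheses, a false rejection under Holm requires the smallest of their p-values to be at most 0.05/m₀. The probability of that is at most m₀ × 0.05/m₀ = 0.05, whatever the correlation.

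**Simulated power.** 32 per arm, three two-sided t-tests, 50,000 trials per row, d = 0.9 at all sites:

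| Correlation | Per site: Bonferroni → Holm | All three: Bonferroni → Holm | At least one (both) |
|---|---|---|---|
| 0 | 0.87 → 0.93 | 0.66 → 0.84 | 0.998 |
| 0.5 | 0.87 → 0.92 | 0.73 → 0.86 | 0.977 |
| 0.8 | 0.87 → 0.91 | 0.78 → 0.88 | 0.942 |

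A separate run of 40,000 trials at correlations 0.3, 0.5 and 0.7 gave 87% → 93%, 92% and 92% per site, and 69%, 72% and 76% → 84%, 86% and 87% for all three. The all-three gain is about 15 points at correlation 0.3 (84 − 69), 11 at 0.7 (87 − 76) and about 8 at 0.9.

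Other assumed effects:
- 0.9/0.6/0.6, correlation 0.5: all three 30% → 48%, each weaker site 48% → 59%.
- 0.9/0.5/0.5, correlation 0 to 0.8: each weaker site 0.33 → 0.42-0.43.
- 0.9/0/0: the responding site has about 0.87 under both.

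**Simulated family-wise error, correlation 0.5.**

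| True effects | Bonferroni | Holm |
|---|---|---|
| 0/0/0 | 4.4% | 4.4% |
| 0.9/0/0 | 3.2% | 4.3% |
| 0.9/0.9/0 | 1.6% | 4.1% |

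The largest value in any null setting was 4.95%, for both procedures.

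**The case against.** The strongest reply is that nothing here is wrong. Section 14.3 prespecifies a recognised correction, gives the reason and controls the type I error. It also has simple matching simultaneous intervals. All of that stands: this is a gain in efficiency, not the repair of an error.

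Four stronger readings are tempting, and none is supported.
- *A reader might infer that Holm's error rate is always the same as Bonferroni's.* It is the same only when no site has an effect. Otherwise Holm spends more of the 5%, as the last table shows, and this is where its extra power comes from. It stays within the limit.
- *A reader might infer that a shared cause of pain makes the loss under Bonferroni greatest.* Effects at all sites do favour Holm. Correlated scores, which a shared cause also implies, reduce its advantage.
- *A reader might infer that Holm repairs the mismatch between sizing at 0.05 and testing at 0.017.* It does not for the first rejection, which still needs p ≤ 0.05/3 and has about 87% power at 32 per group when one site responds. At 35 per arm with nobody lost, that power is 90.2% without Holm.
- *A reader might take the all-three figures as the trial's power.* Section 14.1 adopts no all-sites criterion. If success means any one site, Holm adds nothing to that claim.

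It is also fair to say that the magnitudes rest on assumed site effects and correlations, since section 9.4 gives one effect size from one back pain score, and that the Wilcoxon option was not simulated. The ordering of the two procedures holds for any valid p-values, but the exact percentages are for the t-test.

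**Conclusion.** The point holds as an efficiency improvement. The fixed threshold is valid, and Holm is uniformly at least as powerful with the same guarantee. Under the favourable assumption of d = 0.9 everywhere and correlations of 0.3 to 0.7, Holm adds about 5 to 6 points of power per site and 11 to 15 points for all three. The benefit is confined to the second and third rejections and falls towards zero when only one site responds. The documents do not support a claim that the type I error is mishandled, or that the change makes up for the sample size having been calculated at 0.05.

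**What to change.** In section 14.3, replace the fixed threshold with a statement along these lines: the three site comparisons are tested by Holm's procedure at a family-wise two-sided level of 0.05, with ordered p-values compared with 0.05/3, 0.05/2 and 0.05; day 3 is the primary family, and the same procedure is applied separately within each secondary time point of section 14.2. The secondary time points need to be named, because a sentence on day 3 alone would leave them with no threshold. Exact fractions also avoid the rounding of 0.05/3 to 0.017, which sums to 0.051 over three sites.

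Report Holm-adjusted p-values with each site's mean difference and confidence interval.

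The cost is one sentence, to be settled before any comparison by group, with no extra patients or data. The downside is that simultaneous intervals matching Holm are less simple. The intervals reported should be labelled as unadjusted or Bonferroni, with a note that they may not agree exactly with the Holm decision.
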